### Patient characteristics

In addition to the aforementioned primary and secondary outcomes, several demographic factors and patient characteristics will be assessed at baseline: age, sex, body mass index, socio-economic position, total- or unicompartmental knee arthroplasty, work status (employed or self-employed), knee demanding work, work absenteeism prior to surgery, patient expectations regarding return to work after surgery, work-related knee complaints (i.e. knee complaints during knee demanding activities at work) and self-reported work-relatedness of symptoms. These factors can be adjusted for as potential confounding variables in the analysis.

### Process measures

A process evaluation of the intervention will be conducted according to method described by Linnan and Steckler [48], to identify effective key components of the intervention and/or components that should be improved for further implementation. Data for the process evaluation will be collected using information from the study procedure database, a log of the ikHerstel app and an online patient satisfaction questionnaire that will be administered at 6 weeks and 6 months follow-up. The process measures that will be assessed are shown in Table 3.

**Table 3 Tab3:** Process measures

	**ikHerstel eHealth**	**Goal attainment scaling**	**Case-manager**
**Reach** *The degree of participation*	Eligible participants that were 1) interested in participation and 2) were included and randomized to the intervention or usual care control group^a^ as a percentage of the target population. The estimation of the target population is based on the number of eligible patients that had a consult with their orthopaedic surgeon in the participating centres during the inclusion period		
**Dose delivered** *The proportion of the intervention that was delivered to the patients*	The percentage of patients in the intervention group who received log-in details for the ikHerstel app^a^	The percentage of patients in the intervention group that were invited to make a goal attainment scaling goal before surgery^a^	The percentage of patients in the intervention group who got referred to a case-manager^a^
**Dose received** *The “exposure” and usage of the intervention components*	The percentage of patients in the intervention group that -made a personal recovery plan^b^ -logged in to the ikHerstel app^b^ -completed a recovery monitor^b^ -connected their activity tracker to the app^b^	The percentage of patients in the intervention group that made a work-related goal attainment scaling goal before surgery^a,b^	The percentage of patients in the intervention group that had an appointment with their case-manager before surgery^a,b^
**Patient attitudes** *Patient satisfaction and barriers for the usage of the intervention*	-The mean score that patients rated the ikHerstel app on a 1 – 10 scale^c,d^ -Tabulation of reasons for using and/or not using the ikHerstel app^c,d^	The mean score that patients rated their satisfaction about goal attainment scaling on a scale of 1 – 10^c^	The mean score that patients rated their satisfaction about the appointment with their case-manager on a scale of 1 – 10^c^

^a^study procedure database

^b^log of the ikHerstel app

^c^online questionnaire at 6 weeks follow-up

^d^online questionnaire at 6 months of follow-up

### Costs

An economic evaluation will be executed according to the guidelines of the Dutch National Health Care Institute (Zorginstituut Nederland, 2016). The economic evaluation will be performed from a healthcare and societal perspective. For the healthcare perspective, only costs accruing to the formal Dutch healthcare sector will be considered. For the societal perspective, we will consider costs of the intervention, other healthcare services, occupational healthcare services, informal care, unpaid productivity, absenteeism, and presenteeism.

All relevant costs will be measured using online cost-questionnaires with 3-month recall periods. The cost-questionnaire was developed by our department and tailored to the population and intervention under study. Intervention costs include all costs related to the development, implementation, and execution of the intervention (e.g. ikHerstel, GAS and case-manager) and will be estimated using a micro-costing approach. That is, the cost estimate will be based on actual resources depleted, which will be assessed in detail using prospective data collection, and will be valued in accordance with the Dutch manual for costing studies in health care [49, 50]. Other healthcare costs will consist of costs of primary care (e.g. family physician), secondary care (e.g. hospital stay and visits), and medication (both prescribed and over the counter). The cost of occupational healthcare services will consist of costs of visits to the occupational physician or occupational (physio)therapist. If available, other and occupational health care costs will be valued using Dutch standard costs [50]. If unavailable, prizes of professional health care organizations will be used. Medication use will be valued using prices derived from http://www.medicijnkosten.nl. Informal care will be measured by asking patients to report the number of hours per week they received help from family and friends. Unpaid productivity losses will be measured by asking patients to report the number of hours per week that they were unable to perform unpaid activities (e.g. voluntary work). Unpaid productivity losses and informal care will be valued using a recommended Dutch shadow price [50]. Absenteeism (e.g. total number of sick leave days, measured using a slightly adapted version of the iPCQ [51]) and presenteeism (e.g. lower productivity as compared to normal while at work, measured with the WHO-HPQ [52]) will be valued using sex-specific price weights [50]. Using consumer price indices, all costs will be converted to the same reference year. Because the follow-up period of this study is 12 months, it is not necessary to discount costs and effects.

### Measurements

Digital questionnaires will be administered with the Survalyzer online tool (survalyzer.com), which can be accessed through a link provided via e-mail, to assess all primary and secondary outcome parameters and additional variables at baseline, and 3, 6, 9, and 12 months after surgery. Measurements will be taken from both patients in the intervention and usual care group, regardless of whether they actually followed the intervention (when in the intervention group). The primary outcome parameter and return to work will also be measured every month during the first 6 months. Six weeks after surgery, we will also assess knee functioning (KOOS), pain (VAS), quality of life (EQ-5D-5L) and patient satisfaction. Table 4 shows an overview of our outcome measures, measurement instruments and measurement moments. All relevant costs will be measured using online cost-questionnaires administered at baseline, 3, 6, 9, and 12 months post-surgery.

**Table 4 Tab4:** Outcome measures, measurement instruments and measurement moments

	**STUDY PERIOD**									
**TIMEPOINT**	***t***_***0***_	***t***_***1***_	***t***_***2***_	***t***_***3***_	***t***_***4***_	***t***_***5***_	***t***_***6***_	***t***_***7***_	***t***_***8***_	***t***_***9***_
*** Primary outcome***										
***Quality of life - Duration of return to daily life activities (PROMIS)***	X	X	X	X	X	X	X	X	X	X
*** Secondary Outcomes***										
***Return to Work***		X	X	X	X	X	X	X	X	X
***Physical difficulty experienced at work (WORQ)***	X	X	X	X	X	X	X	X	X	X
***Disease specific functional status (KOOS)***	X		X		X			X	X	X
***Pain Intensity (VAS)***	X		X		X			X	X	X
***Quality of Life (EQ-5D-5L)***	X		X		X			X	X	X
***Energy/Fatique (MFI-20)***	X				X			X	X	X
*** Patient characteristics***										
***Demographics and Patient Characteristics***	X									
*** Process***										
***Patient Satisfaction***			X					X		

T_0_ = baseline, ± 6–8 weeks before surgery; T_1_ = 4 weeks after surgery; T_2_ = 6 weeks after surgery; T_3_ = 2 months after surgery; T_4_ = 3 months after surgery; T_5_ = 4 months after surgery; T_6_ = 5 months after surgery; T_7_ = 6 months after surgery; T_8_ = 9 months after surgery; T_9_ = 12 months after surgery

Patients will have two weeks to complete the questionnaire. After approximately one week, a reminder will be sent by e-mail. If after two weeks the questionnaire is not yet completed, an attempt will be made to contact the patient by phone to encourage them to still complete the questionnaire.

### Statistical analyses

Analyses will be performed in SPSS (effect evaluation) and STATA or R (economic evaluation). All analyses will be performed according to the intention to treat principle. If required, missing cost and effect data will be imputed using multiple imputation according to the MICE algorithm developed by van Buuren and colleagues [53]. To account for the possible clustering of data (with data clustered by surgeon), analysis will be performed using linear multilevel analysis. Accounting for the possible clustering of data is important, as many (economic) evaluations fail to do so, whereas ignoring the possible clustering of data might lead to inaccurate levels of uncertainty and sometimes even biased point estimates [54]. Sensitivity analyses will be performed to test the robustness of the study results. Statistical analyses will be performed according to intention-to-treat principle, which will be compared to per-protocol analyses. Patients will be included in the per-protocol analyses when they used the intervention as intended, which will be defined as having an appointment with their case-manager, defining a GAS goal and generating a personal recovery plan in the ikHerstel app. This will be measured with the study procedure database and a log of the ikHerstel app. Characteristics of the patients measured at baseline will be evaluated and summarized using descriptive statistics.

### Effect analysis

The effect of the intervention on the primary outcome parameter quality of life (i.e. duration until return to activities of daily life, PROMIS-PF) and the secondary outcome time until return to work will be assessed using a multi-level longitudinal Cox proportional hazard model, estimating hazard ratios (HR) and their 95% confidence intervals (95%CI). Multi-level longitudinal linear regression will be used to assess the effect of the intervention regarding all continuous secondary outcomes (e.g. knee functioning, pain intensity, health-related quality of life, physical difficulty experienced at work, and fatigue) estimating betas and their 95% CI. In all models, repeated measurements will be taken into account. We will test the effect of intervention, time and intervention*time. Based on previous literature, several variables will be considered as potential confounders or effect modifying variables, including body mass index, knee demanding work, socio-economic position, work absenteeism prior to surgery, self-reported work-relatedness of symptoms, first primary or second primary knee arthroplasty and the variables used for stratification (unicompartmental- or total knee arthroplasty, participating centres with or without eHealth as usual care, and recovery expectations). Potential confounders will be tested using a forward stepwise selection procedure. If adding the confounder to the model leads to an effect size difference of 10% or more, the variable will be considered as confounder and will be included in the final model. Effect modification will be tested using interaction terms with the intervention (i.e. being/not being in the intervention group). In case of statistically significant interaction terms, analyses will be stratified by the subgroup.

Lastly, we will repeat our analysis to investigate the effect of the intervention on quality of life and return to work within subgroups of patients that, in addition to our intervention, did or did not receive eHealth as usual care from their own hospital or clinic.

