### Randomization and allocation

Included patients will complete a first (baseline) questionnaire approximately eight weeks before surgery. Thereafter, randomization will be performed at the patient level. Randomization will be performed in a 1:1 ratio using computer-based randomization lists in Excel, developed by an independent statistician of the Epidemiology and Biostatistics department of Amsterdam UMC. Randomization will be pre-stratified by medical centre (with or without eHealth as usual care), operation procedure (total- or unicompartmental knee arthroplasty) and recovery expectations regarding return to work [25], either positive: “I expect to be fully back at work earlier than the average knee arthroplasty patient” or negative: “I expect to be fully back at work later than the average knee arthroplasty patient”. Only for the randomization lists for medical centres that do not have eHealth as usual care, block randomization will be used. The allocation sequence is predetermined by the statistician and cannot be altered by the researchers. The randomization will follow the order of receiving the patient’s digital baseline questionnaire. Patients will be blinded to the randomization to either the control- or the intervention group.

After allocation, each patient will receive an e-mail containing instructions and a link and log-in details to either the ikHerstel app or to the eHealth from their own hospital or clinic (as explained below in the intervention paragraph). The research team will inform the medical team of the corresponding centre and, if a patient is allocated to the intervention group, the patient’s case-manager. If any patient refuses or wishes to withdraw from the study, either during the inclusion period or during the study period, they will continue to receive care as usual only.

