### Sample size calculation

We based our sample size calculation on the effect size from a comparable intervention and patient sample [29], and α = 0.05; Power = 80% and an Intraclass Correlation Coefficient (depicting correlation within surgeons) of 0.010. Using a conservative estimation of the effect size, we expected a hazard ratio (HR) of 1.7 and 50% of the patients to return to activities of daily life by the end of the follow-up period in the group who receive our intervention compared to care as usual. Considering this HR, using a 2-sided log-rank test and incorporating clustering of our study (with an estimated 10 patients per surgeon), we need to observe 220 patients. To take 20% dropout into account, we need to recruit 276 patients (i.e. 138 per arm). Agreements were made with all participating centres in which they committed to recruit a certain number of patients, varying between 20 and 80 patients per participating centre.

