### Outcomes

The primary outcome measure of this study will be quality of life, measured with the personalized and reliable, validated and responsive Patient-Reported Outcomes Measurement Information System – Physical Functioning (PROMIS-PF) item bank [20, 41, 42]. A list of 29 activities from the item bank will be presented to the patients at the baseline measurement, from which patients will be asked to select eight activities which are most relevant for them in daily life. By doing this, patients will design their own quality of life short form.

Each activity consists of five functioning levels. Seventeen of the 29 items are scored as: without any difficulty, with a little difficulty, with some difficulty, with much difficulty and unable to do. Twelve items are scored as: not at all, very little, somewhat, quite a lot, and cannot do. At baseline, patients will report their current functioning level. The personalized short form will also be presented to the patients during all follow-up measurements. Post-surgery, successful ‘return to an activity’ is defined by a return to an activity with at least one functioning level higher as compared to the baseline (pre-surgery) functioning level, for instance from ‘with much difficulty’ to ‘with some difficulty’. If patients reach this level, they will be asked at what day they reached this level. Our primary outcome will be defined as the time since surgery to resume six out of the selected eight activities of their own quality of life short form. The secondary outcomes that will be assessed are shown in Table 2.

**Table 2 Tab2:** Secondary outcomes

Return to work	The time (i.e. days, months) between the surgery and the first day back at work, both partly and fulltime
Knee Functioning, measured with The Knee Injury and Osteoarthritis Outcome Score (KOOS) [43]	The KOOS consists of 42 items that assesses five outcomes: pain (9), symptoms (7), activities of daily living (17), sport and recreation function (5), and knee-related quality of life (4) on a 5-point Likert scale (0, no problems – 5, extreme problems). Scores are transformed to a scale of 0 – 100, with 0 representing extreme knee problems and 100 representing no knee problems

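### The time and intervention*time terms are not kept out of the Cox models, so the primary contrast is not fixed; for the continuous outcomes the treatment contrast and the role of baseline are not named

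*Protocol article*

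**What the plan says.** All references are to the Methods of the protocol article.

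- **Primary outcome (Outcomes).** It is one duration per patient: "Our primary outcome will be defined as the time since surgery to resume six out of the selected eight activities". An activity counts as resumed when the patient functions "at least one functioning level higher as compared to the baseline (pre-surgery) functioning level".
- **Primary model (Effect analysis).** The primary outcome and time to return to work "will be assessed using a multi-level longitudinal Cox proportional hazard model, estimating hazard ratios (HR) and their 95% confidence intervals (95%CI").
- **Continuous secondary outcomes (Effect analysis).** "Multi-level longitudinal linear regression will be used to assess the effect of the intervention regarding all continuous secondary outcomes".
- **Terms (same paragraph, directly after both model families).** "In all models, repeated measurements will be taken into account. We will test the effect of intervention, time and intervention*time".
- **Covariates (same paragraph).** "several variables will be considered as potential confounders or effect modifying variables, including body mass index, knee demanding work, socio-economic position", followed by further variables. The baseline value of the outcome is not named. A candidate enters if it changes the effect estimate by at least 10%.
- **Sample size calculation.** "we expected a hazard ratio (HR) of 1.7", with a two-sided log-rank test and 220 patients to be observed.
- **Timing of baseline (Randomization and allocation).** "Included patients will complete a first (baseline) questionnaire approximately eight weeks before surgery. Thereafter, randomization will be performed at the patient level". Table 4 schedules the KOOS, pain, EQ-5D-5L, WORQ and MFI-20 at T0. Return to work has no T0 entry.

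**The concern.** **Cox models.** Monthly questionnaires establish when the event happened; they do not create repeated outcomes. A main effect of time has no meaning in a Cox model, because the baseline hazard absorbs it. An intervention*time term lets the hazard ratio change over follow-up, whereas both the proportional hazards model and the sample size assume one hazard ratio. With three terms to test and none designated, the plan leaves open which number answers the trial's question. One available choice, the intervention coefficient beside the interaction, estimates the effect on the day of surgery and is much less precise.

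**Linear models.** Testing intervention*time is legitimate here, but the meaning of the intervention term depends on how T0 enters and how time is coded. If T0 is a repeated time point and the reference, the intervention main effect is a difference that predates randomisation and has expectation zero. If T0 is left out of the outcome vector, baseline contributes only if it is added as a covariate. The 10% rule does not secure that, because it reacts to chance imbalance rather than to how strongly the baseline value predicts the outcome.

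**Working it through.** **1. Reproduce the planned size.** Inputs from Sample size calculation: HR 1.7, two-sided alpha 0.05, power 80%, ICC 0.010, 10 patients per surgeon, 50% with the event, 20% dropout. The text does not make clear which arm the 50% refers to.

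- Freedman events: (2.7/0.7)² × (1.96 + 0.8416)² = 116.8, so 117.
- Design effect: 1 + 9 × 0.010 = 1.09.
- With 50% events in control, the intervention arm has 1 − 0.5^1.7 = 69.2%, mean 59.6%. Patients: 117/0.596 × 1.09 = 214, within 3% of the stated 220.
- Alternatively, Schoenfeld gives 112 events; with 50% overall and no design effect, 112/0.5 = 224, also within 3%.
- Dropout: 220/0.80 = 275, made even to 276, as stated.

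Both routes use one overall hazard ratio and no time interaction.

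**2. Power of the planned contrast.** Effective events: 220 × 0.596/1.09 = 120.3. SE of the log HR: 2/√120.3 = 0.182. With ln 1.7 = 0.531, z = 2.91 and power = Φ(2.91 − 1.96) = 83%.

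**3. Power of the intervention coefficient when intervention*time is kept.** Assumptions: constant true HR 1.7, exponential times, 12 months of follow-up, linear time measured from surgery. The variance of the coefficient is multiplied by E[t²]/(E[t²] − E[t]²) over the event times. With 50% events in control, E[t] = 5.04 months and E[t²] = 36.9, so the factor is 36.9/(36.9 − 25.4) = 3.2.

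SE: 0.182 × √3.22 = 0.327. z = 1.62, and power = Φ(1.62 − 1.96) = 37%.

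**4. Check by simulation.** 2,000 runs, n = 202 (220/1.09), about 120 events, same assumptions:

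| Cox model | SE of intervention coefficient | Power |
|---|---|---|
| Intervention only | 0.186 | 81% |
| Intervention + intervention*time | 0.340 | 35% |

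The variance ratio is (0.340/0.186)² = 3.3, in line with step 3. In an illustrative delayed effect (HR 1 for 3 months, then 2.2), the intervention-only model had 89% power. The intervention coefficient beside the interaction averaged 0.14 on the log scale, with 7% power.

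**5. Continuous outcomes: meaning of the intervention term.** Illustrative mixed model with linear time, T0 as a repeated value, 220 patients and 60 runs. A benefit of 6 points at every post-surgery visit gave an intervention coefficient of 3.5. A benefit growing linearly to 6 points at 12 months gave about 0 (−0.1), with the effect in the interaction (0.49 per month × 12 = 5.9). The same term therefore means different things under different patterns of benefit.

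**6. Continuous outcomes: value of baseline as a covariate.** With rho the baseline-to-follow-up correlation (not given in the document, so assumed), the relative variances are 1 with baseline unused, 2(1 − rho) for a change contrast, and 1 − rho² with baseline as covariate. The gain against a change contrast is (1 − rho²)/(2(1 − rho)) = (1 + rho)/2.

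| rho (assumed) | Against baseline unused, 1 − rho² | Against change contrast, (1 + rho)/2 |
|---|---|---|
| 0.3 | 0.91 | 0.65 |
| 0.5 | 0.75 | 0.75 |
| 0.7 | 0.51 | 0.85 |

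**The case against.** The section says that these effects will be tested. It does not say that the intervention coefficient from a model retaining the interaction is the reported result. The same section commits the primary outcome to a proportional hazards model that estimates hazard ratios, which fits one overall HR with the interaction as a side check. The phrase about all models also belongs grammatically to the sentence on repeated measurements. This stands in part: a reader might infer that the trial has only 35-37% power for its primary outcome, and the text does not support that. The figure applies to one permitted reading, and it depends on coding: with time centred at the mean event time the same formula gives an inflation of 1. What the objection does not supply is any wording that limits the time terms to the linear models or designates the primary contrast.

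A reader might also infer that baseline values will go unadjusted. The text does not say so. The covariate list is open, T0 may enter as a repeated measurement, and an analysis plan that is not shown may settle this. Nor does the point reach the primary outcome, whose event is already defined against baseline, or return to work, which has no T0 value.

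For the linear models, intervention*time can carry the treatment effect, and the plan does test it. That specification is standard; what is missing is the named contrast.

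Finally, a reader might place the 50% in the intervention arm and arrive at lower powers. Under Freedman with the design effect, that setting needs 306 patients, so it does not correspond to the plan's 220.

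**Conclusion.** The point holds in a limited form. As worded, the time and intervention*time terms extend to the Cox models, where they conflict with one event time per patient, with the proportional hazards model and with the single hazard ratio behind the sample size. The primary contrast is therefore not fixed.

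The possible loss is large but conditional: power drops from about 81-83% to about 35-37% only if the intervention coefficient is read from a Cox model that keeps a linear, uncentred interaction, under HR 1.7, exponential times and about 120 effective events.

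For the continuous secondary outcomes, the weakness is an unnamed contrast and no assured use of the baseline value. The size of that loss cannot be fixed from the document because it gives no correlation. The plan should be corrected, but it does not follow that the trial is underpowered or that its hypothesis goes untested.

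**What to change.** - **Primary outcome and return to work.** State that the result is one treatment hazard ratio, with its 95% CI, from the multilevel Cox model (patients within surgeons) without a time interaction. Use intervention*time there only as a check of proportional hazards.
- **Continuous secondary outcomes.** Limit the time and intervention*time terms to these models. Take post-surgery values as the outcome, enter the baseline value of the same measure as a fixed covariate outside the 10% rule, and name the treatment contrast: the adjusted difference at a stated visit, averaged over follow-up, or both.

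The cost is a few sentences in the protocol or analysis plan, settled before the data are analysed by arm. The T0 values are already scheduled, so no new data, visits or patients are needed.

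### The primary Cox model's covariates are chosen by a 10% change in the treatment effect on no stated scale, and a significant interaction splits the analyses with nothing said to keep the overall HR primary

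*Protocol article*

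**What the plan says.** The primary outcome (time to resuming six of eight chosen activities) is analysed with a multi-level Cox model. Its covariates are not named. Under Effect analysis, "several variables will be considered as potential confounders or effect modifying variables, including body mass index" opens the candidate list. Six baseline variables are named ("body mass index, knee demanding work, socio-economic position, work absenteeism prior to surgery, self-reported work-relatedness of symptoms, first primary or second primary knee arthroplasty"), followed by "the variables used for stratification (unicompartmental- or total knee arthroplasty, participating centres with or without eHealth as usual care, and recovery expectations". That makes nine, and the wording leaves the list open. Under Patient characteristics a wider set, including age and sex, is recorded, and "These factors can be adjusted for as potential confounding variables in the analysis".

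Selection is then prescribed: "Potential confounders will be tested using a forward stepwise selection procedure". The entry criterion is: "If adding the confounder to the model leads to an effect size difference of 10% or more, the variable will be considered as confounder". For effect modification, "Effect modification will be tested using interaction terms with the intervention", and the consequence is: "In case of statistically significant interaction terms, analyses will be stratified by the subgroup".

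The section gives no scale for the 10%, no significance level for the interactions and no multiplicity control. It does not say which model or which estimate is primary.

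**The concern.** Allocation is randomised 1:1 within strata, so any baseline imbalance is due to chance. A change-in-estimate rule therefore does not detect confounding. It picks up chance imbalance and, in a Cox model, the shift in the HR that follows from adding any prognostic covariate even when the arms are perfectly balanced (non-collapsibility). It also consults the treatment estimate in order to choose the model that will report that estimate.

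The randomisation is stratified on eHealth centre, procedure and recovery expectations. The limitations section relies on the eHealth stratification to deal with variation in usual care. Yet all three factors can be absent from the model.

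The interaction rule adds a second dependence on the data: a chance result decides whether the analyses are presented by subgroup. At stake is whether a reader can know, before the data are analysed, which HR will be the trial's result.

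**Working it through.** **The plan's own figures.** The plan gives no error rate for the selection rule, so there is none to reproduce. Its sample size (220 observed, 276 recruited) serves below only to set the size of a simulated trial. Freedman's formula with 50% events in the control arm (mean event proportion 0.596) gives 117/0.596 × 1.09 = 214, within 3% of 220. Other readings of the 50% run from 205 to 306. 220/0.8 = 275, or 276 for equal arms. Nothing below depends on which reading is right.

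**Step 1: what 10% means on each scale.**
- Estimate at HR 1.05 (log 0.0488). On the log scale a shift of 0.0049 is enough, so moving from 1.050 to 1.055 admits a covariate. On the HR scale the estimate must reach 1.155.
- Estimate at HR 1.70 (log 0.531). On the log scale the threshold is a shift of 0.053, that is to about 1.61 or 1.79. On the HR scale it is 1.53 or 1.87.

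The log-scale rule becomes very easy to satisfy as the effect approaches the null; the HR-scale rule does not.

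**Step 2: how often covariates enter.** Simulation with 220 patients, 50% events, no clustering and 600 runs per row. There are nine independent covariates: eight binary with log-HR ±g and one continuous with log-HR g/2 per SD. The values of g are assumptions. Each step compares with the current model.

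| True HR | Scale | g | At least one enters | Mean number |
|---|---|---|---|---|
| 1.0 | log HR | 0.3 | 94% | 4.6 |
| 1.0 | log HR | 0.5 | 99% | 6.4 |
| 1.0 | HR | 0.3 | 3% | 0.03 |
| 1.7 | log HR | 0.3 | 53% | 1.0 |
| 1.7 | log HR | 0.5 | 76% | 2.2 |
| 1.7 | HR | 0.3 | 6% | 0.06 |

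The HR scale was run only at g = 0.3. A second simulation (nine binary covariates, assumed log-HRs 0 to 0.6, 1,500 runs) gave 10% at the null and 14% at HR 1.7 on the HR scale.

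**Step 3: effect on the reported HR.** At a true conditional HR of 1.7 the average estimate was 1.57-1.66 unadjusted, 1.67-1.70 after selection and 1.73-1.75 with all nine covariates.

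**Step 4: error rates.** At the null, rejection was 4-5% unadjusted, 5-7% after selection and 5-7% with all nine covariates fixed (Monte Carlo SE about 1 point). The second simulation gave 5.0% unadjusted, 5.4% (HR scale) and 5.8% (log scale) after selection, and 5.7% fixed. Power at HR 1.7 was 75-77% after selection and 77-79% with all nine fixed.

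**Step 5: interactions.** With k independent tests at 0.05 and no true effect modification, P(at least one significant) = 1 − 0.95^k.
- k = 9: 1 − 0.95^9 = 0.370.
- k = 12: 1 − 0.95^12 = 0.460.

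The simulation in Step 2 gave 35-39% for nine.

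**Step 6: what a split leaves.** Schoenfeld power is Φ(√(d/4) × ln HR − 1.96), ignoring clustering.
- d = 110: Φ(5.244 × 0.531 − 1.96) = Φ(0.82) = 79%.
- d = 55 (equal halves): Φ(3.708 × 0.531 − 1.96) = Φ(0.01) = 50%.

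This assumes HR 1.7 in both halves, which is the relevant case when the trigger was false.

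**The case against.** **The scale can be inferred.** The sample size section calls its HR the effect size, and the Cox model estimates HRs. On that reading the rule seldom fires and the primary model is mostly the unadjusted one. This is the strongest reply, and it rules out saying that covariates will usually be selected. It does not settle the matter. The rule is not tied to that section, and it follows text on secondary outcomes estimated as betas. If it is read on the HR scale, the stratification factors are nearly always left out: with any covariate entering in 6% of runs at HR 1.7, they are absent in at least 94% (at least 86% using the 14% figure).

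**The procedure is stated in advance and the analysts are blinded.** Both are true, and they limit deliberate choice. But the 10% comparison can be run on masked group labels, and a stated algorithm with an open list and no scale does not fix the model.

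**The split may be additional.** A reader might infer that a significant interaction withdraws the overall HR. The text does not say so, and the separately planned eHealth subgroup analysis is described as a repeat of the main one. What stands is narrower: nothing states that the overall HR remains primary.

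**The interaction count is an assumption.** The section does not plainly say that all nine variables are tested as modifiers, and it gives no significance level. The 37% is conditional on both, and on independence.

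**Conclusion.** The point holds as a badly fixed rule. It is not a matter of detail left to an analysis plan, because the protocol itself prescribes the selection and the split. The adjusted set depends on the data and, through the unstated scale, on the analyst's reading: 94-99% against 3% of null trials with at least one covariate entered, under assumed covariate effects. The reported HR moves with it, and the stratification factors have no secured place. The chance of at least one false interaction trigger is about 37%, for nine independent tests at an assumed 0.05 with no true effect modification.

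Three stronger readings are not supported:
- **Inflated type I error from selection.** The fixed nine-covariate model rejects at a similar rate, so no material inflation is shown.
- **A reliable power loss.** The differences are small and rest on assumed covariate effects, and the comparison is with a nine-covariate model, not the shorter one recommended here.
- **A 60% false-trigger rate over the primary outcome and return to work** (1 − 0.95^18). Both outcomes come from the same patients, so the tests cannot be treated as independent.

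**What to change.** Replace the selection and interaction sentences under Effect analysis with text to this effect:

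- The primary model contains randomised group, the three stratification factors and a short named list of prognostic baseline covariates fixed before unblinding (for example body mass index, knee-demanding work and absenteeism before surgery), with the surgeon-level clustering already planned.
- No covariate is selected by its effect on the treatment estimate.
- The overall adjusted HR is always the primary result.
- Interaction and subgroup analyses are exploratory, all are reported, and none replaces the overall estimate.

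The cost is small. The stratification factors are known at randomisation and the example covariates are already recorded at baseline, so only wording changes. The model uses a few more degrees of freedom, and the HR must be described as conditional on the fixed covariates. The change should be made and dated before unblinding, since a later choice could not be shown to be independent of the results.
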